### Statistical analysis

The main analysis will focus on all randomly assigned patients (intention-to-treat analysis). The alpha risk is 5% and the power is 90%. Given the main variables studied, there will be no missing data for analysis of the primary outcome. The descriptive statistical analysis will include the following for each quantitative parameter at each time: average, standard deviation, minimum, maximum, median and quartiles, and number of missing values. The categorical variables will be expressed by the frequency of distribution and the associated 95% bilateral confidence intervals. For the primary endpoint, which is theoretical length of hospital stay, the two groups will be compared by using Student’s *t* test if, as suggested by a preliminary study, the distribution of the variable does not deviate significantly from a Gaussian distribution; otherwise, a Mann–Whitney test will be used. For the secondary endpoints, the categorical criteria will be analyzed by using a chi-squared test. In the event that the chi-squared validity criteria are not verified, an exact probability test will be used. Quantitative secondary criteria will be compared by *t* test or Mann–Whitney according to their distribution in the sample considered. All tests will be bilateral at risk of the first species set at 5%. The analysis will be performed by using IBM SPSS Statistics, version 20 software (IBM, Armonk, NY, USA).

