## Objectives

The primary objective is to determine whether low-pressure (7 mm Hg) instead of standard-pressure (12 mm Hg) pneumoperitoneum for patients undergoing laparoscopic colonic resection results in a reduced length of hospital stay of at least 1 day. The secondary objectives are the comparison between groups of post-operative pain, analgesics consumption, 30-day post-operative morbidity, operative time, bleeding, quality of visibility during intervention, conversion rate, perioperative cardiovascular and respiratory function, time to passage of flatus and stool, time to sitting out and mobilizing, and quality of oncological resection (lymph node dissection and curative resection).

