### Consent and randomization

During the pre-inclusion visit, the investigator will inform the participant and answer all questions regarding the purpose, nature of, foreseeable risks, and the expected benefits of the clinical trial. The investigator is responsible for obtaining informed consent from the participant. An original copy of the information note and signed consent will be given to the patient. The other original copy will be retained by the investigator as part of the study documents in an area inaccessible to third parties. After the written consent of the patient is obtained, randomization will take place the day before or the day of the procedure but at the latest before the incision. When an investigator (“operator” surgeon) wishes to perform the randomization/inclusion after verifying the eligibility of the participant, they will send a randomization application document to the statistician of the study, who will send back a patient number (of three digits corresponding to the inclusion rank), an anonymous letter code (four letters), and the result of the randomization arm, namely group A (experimental): insufflation at low pressure (5–7 mm Hg) or group B (control): insufflation at standard pressure (12–15 mm Hg). The two groups will be balanced with a ratio of 1:1. Randomization will be performed by using the following method: for each subject entering the study, a number K between 0 and 9 will be drawn randomly from Excel. The subject will be assigned to the control group if K is 0 or even or to the “low pressure” group if K is odd. Simple randomization does not necessarily lead to homogenous groups. However, a deviation of less than 20% should have little effect on power loss, and the groups should equilibrate with larger sample sizes (more than 50).

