### Outcomes

The primary outcome is to determine whether low-pressure (7 mm Hg) instead of standard-pressure (12 mm Hg) pneumoperitoneum during laparoscopic colonic resection leads to a reduction of the length of hospital stay of at least 1 day. The theoretical discharge date is the date of medical discharge of the patient, evaluated daily between 7 and 8 a.m., in accordance with predefined criteria, which are no pain requiring the use of analgesics more than stage 2, no nausea or vomiting, no fever of more than 38 °C, resumption of a normal diet, transit (passage of flatus/stool), patient mobilization, and patient acceptance. The real discharge date is the date of discharge including a possible continuation of hospitalization for non-medical reasons (i.e., waiting for convalescent home, personal suitability of the patient).

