### Sample size

The calculation of the number of subjects required is based on the primary endpoint, which is a decrease in hospital length of stay of at least 1 day in patients operated on laparoscopically for malignant or benign colonic pathology using a low-pressure pneumoperitoneum with the medical insufflation device AirSeal®. The activity of the Colorectal Unit of the Magellan Medico-Surgical Centre was 170 colonic laparoscopic resections in 2017, and the average hospital stay of patients in this control arm would be 5 ± 2 days based on available data. As such, in unilateral formulation, to show a difference (1 day) with an alpha risk of 5% and a power of 90%, there should be 69 patients recruited per group, resulting in a total of 138 patients.

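### The primary objective asks for a reduction in stay of at least 1 day, but the sample size and primary test address only a difference from zero, and the choice of test is left to a distribution check

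*Protocol article*

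**What the plan says.** The Objectives section asks whether low pressure "results in a reduced length of hospital stay of at least 1 day". The Outcomes section repeats this as the primary outcome: whether it "leads to a reduction of the length of hospital stay of at least 1 day". The Sample size section also describes the primary endpoint as a decrease of at least 1 day, and then treats 1 day as the difference to detect: "in unilateral formulation, to show a difference (1 day) with an alpha risk of 5% and a power of 90" per cent. The planning values are "the average hospital stay of patients in this control arm would be 5 ± 2 days based on available data", and the result is that "there should be 69 patients recruited per group, resulting in a total of 138 patients".

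The Statistical analysis section makes theoretical length of stay the primary variable. Student's t test is used "if, as suggested by a preliminary study, the distribution of the variable does not deviate significantly from a Gaussian distribution"; otherwise Mann–Whitney is used. All tests are two-sided at 5%. No margin, shifted null hypothesis or confidence-interval rule is tied to 1 day, and the distribution check is not named. The section does plan means, SDs, medians and quartiles for every quantitative variable. Under Outcomes, fitness for discharge is assessed once a day, so stay is recorded in whole days.

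**The concern.** The stated question and the planned test differ. The question concerns a minimum size of effect; the test asks only whether the effect differs from zero. Someone who reads the objective literally and then sees p < 0.05 could take the 1-day claim as established when the estimate is well below 1 day.

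A second, smaller matter is that the primary analysis is not fixed in advance. If the check rejects, the primary test becomes a rank comparison. That test does not estimate a difference in mean days, which is the scale of the objective and of the sample size, and no effect estimate in days is tied to that branch. What the primary result measures then depends on the data.

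**Working it through.** **Inputs.** Difference 1 day, SD 2 (reading the ± figure as an SD), one-sided alpha 5%, power 90% and 69 per group come from Sample size. Two-sided 5% testing comes from Statistical analysis. Allocation is 1:1 ("The two groups will be balanced with a ratio of 1:1", Consent and randomization). No loss is allowed for ("there will be no missing data for analysis of the primary outcome", Statistical analysis).

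**1. The plan's own figure.** n per arm = 2 × SD² × (z₁₋α + z₁₋β)² / Δ² = 2 × 4 × (1.645 + 1.282)² / 1² = 68.5, rounded up to 69. The stated 69 is reproduced with a null of 0 and an alternative of 1 day. It is not the size for a null of 1 day.

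**2. Where significance starts.** SE = 2 × √(2/69) = 0.3405 and t(0.975; 136 df) = 1.978, so the threshold is 1.978 × 0.3405 = 0.67 day.

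| Observed reduction (days) | 95% CI (days) |
|---|---|
| 0.67 | 0 to 1.35 |
| 1.00 | 0.33 to 1.67 |
| 1.67 | 1.00 to 2.35 |

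**3. How often a significant result goes with less than 1 day.** Using the noncentral t distribution with 136 df:
- True reduction 0.5 day (noncentrality 0.5/0.3405 = 1.47): significant in 31% of trials.
- True reduction 0.75 day (noncentrality 2.20): significant in 59% of trials.
- True reduction exactly 1 day: significant with an observed reduction below 1 day in Φ(0) − Φ((0.673 − 1)/0.3405) = 0.50 − 0.17 = 33% of trials (normal approximation).

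**4. If the objective is taken literally** (null: reduction of 1 day or less), a true reduction of exactly 1 day is declared only at the error rate: 5% one-sided, or 2.5% in the favourable direction two-sided. For 90% power, n per arm = 2 × 4 × (z₁₋α + z₁₋β)² / (true − 1)². The true reduction is an assumption here, because the document gives none:

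| Assumed true reduction (days) | One-sided 5% | Two-sided 5% |
|---|---|---|
| 1.25 | 1097 | 1345 |
| 1.5 | 275 | 337 |
| 2 | 69 | 85 |
| 2.5 | 31 | 38 |

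**5. The switch.** The shapes and the check are assumptions: whole-day stays, control mean 5, SD 2, 69 per arm, switching when either arm is rejected at 5%.
- With Shapiro–Wilk and stays floored at 1 day, the switch occurred in about 93% to 100% of simulated trials for rounded normal, gamma and lognormal shapes.
- With rounded normal stays (means 5 and 4, no floor), it occurred in about 82% with Shapiro–Wilk, 99% with Lilliefors, 24% with uncorrected Kolmogorov–Smirnov and 11% with a skewness–kurtosis test.
- With gamma or lognormal stays at the same means, it occurred in 83% to 100% across all four checks.
- Type I error of the two-stage procedure (Shapiro–Wilk) was 4.3% to 5.2%.
- Power at a 1-day effect, t test against Mann–Whitney: 82% against 80% (rounded normal), 81% against 86% (gamma), 82% against 92% (lognormal).

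**The case against.** The strongest reply is that the document shows how 1 day is meant. Sample size uses it as the difference to detect, 69 per group follows exactly from a null of zero, and the Abstract describes the primary outcome simply as a comparison of stay between groups. On that reading the design is coherent and only the wording of the objective is loose. This stands, and it is why the remedy is rewording and not a new sample size.

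A reader might infer more than the document supports:
- *That the trial can never support a 1-day claim.* It can, if the observed reduction is about 1.67 days or more; the interval is computable from the planned means and SDs.
- *That any p < 0.05 will be reported as meeting the 1-day objective.* No such decision rule is written. The gap is that nothing excludes it.
- *That the result might not be available in days.* Mean stay per arm is planned whichever test is used. What is missing is a designated primary estimate in days for the Mann–Whitney branch.
- *That the switch inflates type I error.* The simulations show no inflation.
- *That Mann–Whitney is almost certain to become primary.* This depends on the check, which is unnamed, and on the shape. The protocol cites a preliminary study suggesting a Gaussian distribution, which is not shown.

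It is also fair that both tests are valid and prespecified, and that a rank test may be more powerful under skew. That is a cost of the remedy; it does not justify leaving the choice to the data.

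**Conclusion.** The mismatch is real but moderate. The objective, the outcome definition and the endpoint wording in Sample size ask for at least 1 day; the test and the 69 per arm address a difference from zero. Significance alone is reached from an observed 0.67 day, a full day short of the 1.67 days at which the 95% lower limit reaches 1 day. These figures assume SD 2 in both arms, 69 analysed per arm and the stated two-sided 5% level.

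The switch is a secondary point. Its harm is a primary quantity left to the data, not a wrong error rate. For a whole-day and probably skewed stay it will often lead to the rank test, with the frequency depending on the check and the true shape.

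This should be corrected because it governs what a positive result may claim. It is not a fatal flaw, since 1 day can be read as the planning difference.

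A related but separate inconsistency is that the sample size is one-sided and the analysis two-sided. Two-sided testing with 90% power needs 85 per arm (170 in total), and 69 per arm gives about 83%.

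**What to change.** Before the database is frozen:

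1. In Objectives, Outcomes and Sample size, state the question as whether low pressure reduces length of stay, with 1 day as the planning difference.
2. In Statistical analysis, name one primary analysis: the difference in mean theoretical stay in days with a two-sided 95% CI, for example by Welch's method. Remove the normality switch and keep Mann–Whitney as a sensitivity analysis.
3. Add that a reduction of at least 1 day is concluded only if the lower confidence limit is 1 day or more.

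This costs wording only, with no added patients or data. The downside is lower power than a rank test if stay is strongly skewed: about 81% to 82% against 86% to 92% in the simulated gamma and lognormal cases. If the sponsor instead wants the literal question tested, the sample size must be derived afresh from a stated true reduction larger than 1 day.

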### Trial status

The protocol number is ID-RCB: 2018-A03028–47, version n°2.0 from 07/01/2020 promotor code: CHUBX 2018/42. The first inclusion was on January 7 2019; the trial was scheduled to end around Sept 7, 2020. The inclusion period is 18 months with 2 months of participation for the patient.

## Data Availability

Data analysis will be performed by the principal investigator. This analysis will result in a written report which will be submitted to the sponsor, who will forward it to the Committee for the Protection of Persons and to the competent authority. Any written or oral communication of the results of the research must receive the prior agreement of the coordinating investigator and, where appropriate, of any committee set up for the research. The coordinating investigator undertakes to make available to the public all negative and inconclusive and positive research results. In accordance with the law n ° 2002–303 of March 4, 2002, the participants will be informed, at their request, of the overall results of the research. The results of this study will be published in peer-reviewed journals and be presented at national and international conferences.

## Abbreviations

CO_2_: Carbon dioxide
TOF: Train of Four
